# Effect of maternal oxygen supplementation for parturient undergoing elective cesarean section by high-flow nasal oxygen compared with room air on fetal acidemia: study protocol for a randomized controlled trial

**DOI:** 10.1186/s13063-024-07927-y

**Published:** 2024-01-22

**Keywords:** Oxygen, High-flow nasal oxygen, Fetal acidemia, Umbilical arterial lactate, Intrauterine resuscitation, Cesarean section

## Abstract

**Background:**

Maternal oxygen supplementation is usually used as an intrauterine resuscitation technique to prevent fetal hypoxia and acidemia during delivery. However, there has been a great deal of controversy regarding the effects of prophylactic maternal oxygen during cesarean section, during which the incidence of fetal acidemia seems to be higher compared with that during labor. High-flow nasal oxygen (HFNO) can improve oxygenation better in patients with high-flow oxygen airflow. The purpose of this study is to determine whether maternal oxygen supplementation with HFNO has a positive effect on fetal acidemia during cesarean section through umbilical arterial blood gas analysis.

**Method:**

This prospective, single-center, randomized, double-blinded trial will enroll 120 patients undergoing cesarean section. Participants will be randomly assigned to the HFNO group or air group at a 1:1 ratio. For parturients in the HFNO group, the flow rate is 40L/min, and the oxygen is heated to 37℃ with humidity 100% oxygen concentration through the Optiflow high-flow nasal oxygen system. And for the air group, the flow rate is 2 L/min with an air pattern through the same device. The primary outcome was umbilical artery (UA) lactate. Secondary outcomes include UA pH, PO_2_, PCO_2_, BE, the incidence of pH < 7.20 and pH < 7.10, Apgar scores at 1 and 5 min, and neonatal adverse outcomes.

**Discussion:**

Our study is the first trial investigating whether maternal oxygen supplementation with HFNO can reduce the umbilical artery lactate levels and the incidence of fetal acidemia in cesarean section under combined spinal-epidural anesthesia.

**Trial registration:**

ClinicalTrials.gov NCT05921955. Registered on 27 June 2023.

**Supplementary Information:**

The online version contains supplementary material available at 10.1186/s13063-024-07927-y.

## Introduction

Maternal oxygen supplementation has been widely used for intrauterine resuscitation intervention in the clinic to prevent neonatal acidemia. Previous studies have reported that maternal hyperoxygenation has a positive effect on fetal heart rate pattern during the second stage of labor in the presence of suspected fetal distress [1], and is associated with a low overall rate of the composite neonatal adverse outcome [2].

However, fetal acidemia is more likely to occur during a cesarean section than during labor. The functional residual capacity and reserve oxygen capacity of pregnant women are decreased by uterine migration and obesity, and these changes are worsened in the supine position. Moreover, maternal oxygen consumption is increased by fetal and placental metabolism. In addition, spinal block-induced sympathicolysis decreases maternal systolic arterial blood pressure, causing hypoxia and anaerobic metabolism in infants [3]. Previous study suggests that the indication of cesarean section is also a risk factor of fetal acidemia [4].

Studies focused on the effect of maternal oxygen supplementation during cesarean section have shown mixed results. Prior researches demonstrated that maternal oxygen improved PaO_2_ in the umbilical artery (UA) [5–8]. A prospective trial observed higher UA pH values in the receiving oxygen group [9]. Moreover, a recent meta-analysis specifically assessing the use of supplemental oxygenation at the time of cesarean delivery concluded that oxygen supplementation was associated with lower rates of UA pH less than 7.2 [10]. But, several trials have shown that maternal oxygenation had no effect on UA pH [8, 11, 12] and fetal wellbeing [13].

In the previous trials, the concentrations and flow of oxygen inhalation were inconsistent. The maximum oxygen flow rate was not more than 10 L/min [7]. It has been demonstrated that providing 35% oxygen via a facemask does not significantly improve fetal oxygen delivery during cesarean section under spinal anesthesia [14]. But 60% supplementary oxygen increased fetal oxygenation [6, 8]. Therefore, the different concentrations and flows may have different effects.

The high-flow nasal oxygen (HFNO) has been widely used in clinical practice, which provides humidified warm oxygen at a high flow rate, thus generating low positive airway pressure, and improving oxygenation and comfort [15]. HFNO has been safely used in pre-oxygenation of general anesthesia for women in labor [16, 17], providing superior oxygenation during rapid sequence induction compared to standard facemask [17]. However, most of those studies focused on maternal effects, few studies evaluated fetal indicators as the primary outcome.

The aim of this study was to investigate the immediate fetal effects of supplemental oxygenation with HFNO by measuring umbilical arterial blood gas values at the time of term, elective cesarean section. We hypothesized that such supplementation would have a positive effect on umbilical artery lactate levels, a marker of metabolic acidosis and neonatal morbidity.

## Method

### Study design

This trial is a parallel, prospective, single-center, randomized controlled trial. Using a difference test, we focus on the effect of maternal supplemental oxygenation with HFNO on the fetus compared with room air. The study will be performed at Beijing Tongren Hospital, Capital Medical University. And we will adhere to the Good Clinical Practice guidelines and the Declaration of Helsinki during the entire study. The protocol of this trial was approved by the Clinical Research Ethics Committee of Beijing Tongren Hospital on March 9, 2023, with the latest vision 3.0 (approval NO.TREC2023-KY021). This trial has been registered on ClinicalTrials.gov (identify: NCT05921955). Any important protocol modifications will be submitted to the ethical committee for approval. The SPIRIT 2013 checklist is listed in additional file 1.

### Participants

We will recruit 120 patients scheduled to undergo elective cesarean section in the Beijing Tongren Hospital. One trained researcher will screen the eligible patients, explain all the details, and sign the informed consent before the day of surgery. The flowchart of the study is illustrated in Fig. 1, and the SPIRIT figure of enrollment, interventions, and assessments is presented in Table 1.

**Fig. 1 Fig1:**
[figure not shown]
Flowchart of the study

**Table 1 Tab1:** Standardized Protocol Items: Recommendations for Interventional Trials (SPIRIT) schedule for enrolment, intervention, and assessment

	Study period				
	Enrollment	Allocation	Post-allocation		
	The day before the surgery	The surgery day	End of injection to delivery	Baby born	Discharge
Enrollment					
Enrollment	X				
Informed consent	X				
Allocation		X			
Intervention					
Intervention			X		
Assessments					
Maternal Information	X	X	X	X	X
Intraoperative situation			X		
UA blood gas analysis				X	
Newborn outcome				X	X

### Inclusion criteria

Participants who meet all the following criteria will be enrolled:An elective cesarean section at Beijing Tongren HospitalGestational age ≥ 37 weeksAged 18 to 45 years oldAmerican Society of aAnesthesiologists (ASA) classification I–IIIPatients fasted for 6–8 h, and the water restriction time was ≥ 2 h.Anesthesia: combined spinal-epidural anesthesiaAgree to the study and sign the informed consent

### Exclusion criteria

Participants will be excluded if they have any of the following conditions:Fetal or placental abnormalities are known(premature rupture of membranes, severe intrauterine distress, and fetal malformation)Maternal with complications (eclampsia or cardiovascular or cerebrovascular disease)Maternal BMI ≥ 40 kg/m.^2^Difficult intubation history or known difficult airwayContraindications for HFNO such as nasal lesions or structural changesGastroesophageal reflux disease

### Randomization and blinding

Randomization will be conducted by a computer-generated blocked randomization sequence. All participants conforming to the inclusion criteria are randomly assigned to the HFNO group or the air group at a ratio of 1:1. And the random numbers are placed in opaque envelopes and arranged in serial numbers, which are kept by an anesthesia technician. On the day of surgery, the envelope will be opened by the anesthesia technician when the patients enter the room and the grouping result can be obtained. Others are unaware of the group information.

Unblinding will only be allowed when serious adverse effects occur. Participants will be distributed and assigned in numerical order. The outcome will be assented by assessors, and the data will be calculated by statisticians who will not participate in the treatment. All original records including informed consent and CRF together with related letters will be reserved for 10 years and then destroyed according to the hospital standards.

### Intervention

Participants will be monitored with electrocardiograph (ECG), pulse oxygen saturation, and non-invasive blood pressure after entering the room. Heart rate (HR), systolic blood pressure, and diastolic blood pressure were recorded every minute in the supine position. A 22G intravenous cannula will be inserted in the dorsum of a hand. All the patients will receive an intravenous 500 ml of Ringer’s lactate solution.

Combined spinal-epidural anesthesia will be performed at the L2–3 or L3–4 with the patient in the right lateral position. The anesthesiologist determined the local anesthetic dose of ropivacaine (12–15 mg) according to the height of the parturient. After injection of the local anesthetic solution, a 19G terminal closed epidural catheter will be placed. At the same time, oxygen will be supplied to patients in the HFNO group. The flow rate of 40 L/min heated to 37℃ with humidity 100% oxygen concentration is delivered through the Optiflow high-flow nasal cannula system. And the patients of the air group receive the 2 L/min with air pattern through the same device.

The patient is immediately placed in the supine position once the anesthesia procedure is completed with a left lateral table tilt of 15°. The upper level of the sensory block will be assessed in the midline, using a pin to test for the absence of touch sensation.

HR and blood pressure will be recorded every minute following the injection of the spinal drug until the baby is delivered. The vasopressor bolus is administered as soon as the hypotension is occurred. If hypotension is not corrected after 1 min, then additional boluses will be administered every minute until hypotension is corrected (HR ≥ 75 bpm, 50 μg of phenylephrine boluses; HR < 75, 6 mg of ephedrine boluses).

Umbilical arterial and venous blood samples will be obtained for blood gas analysis from a segment of the umbilical cord double-clamped before the baby’s first breath.

### Outcome assessment

The primary outcome is UA lactate levels. The secondary outcomes include UA pH, PO_2_, PCO_2_, BE, the incidence of pH < 7.20 and pH < 7.10, Apgar scores at 1 and 5 min, and the neonatal adverse outcomes in the operating room and ward (such as intubation, mechanical ventilation, and admission to neonatal unit). Others include the number of hypotensive episodes, the number of vasopressor boluses required, the incidence of tachycardia, bradycardia, arrhythmias, the time from subarachnoid injection to skin incision, the time of oxygen supplementation, and the time from skin incision to fetal delivery.

### Sample size calculation

According to a retrospective observational study, there was a strong inverse correlation between lactate and pH (*r* =  − 0.77, *p* < 0.001) [18], and the clinically significant change of UA pH is assumed to be 0.02 pH units [19]. According to the experience of our hospital, the mean of the UA lactate is 2.0 (0.028) mmol/l. With a probability of *α* = 0.05, *β* = 0.2, and power of 0.80, the sample size was 53 according to a 2-side 2-sample equal-variance *t* test. Considering 15% patient loss, we are going to recruit 120 patients. The sample size was calculated with PASS software.

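### The 53 per arm appears to rest on 0.77 × 0.02 used as a lactate difference; a correlation is not a slope, so the 80% power claim for UA lactate is unsupported

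*Protocol article*

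**What the plan says.** Under Outcome assessment the protocol article says: "The primary outcome is UA lactate levels". The trial is therefore powered, or meant to be powered, on a quantity in mmol/L.

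Under Sample size calculation it gives these inputs:

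- From an outside retrospective study, "there was a strong inverse correlation between lactate and pH", with r = −0.77.
- From another source, "the clinically significant change of UA pH is assumed to be 0.02 pH units".
- From the hospital's own experience, "the mean of the UA lactate is 2.0 (0.028) mmol/l". The bracketed figure is not labelled.
- Alpha 0.05, beta 0.2 and power 0.80.

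The result is that "the sample size was 53 according to a 2-side 2-sample equal-variance" t test, and then "Considering 15% patient loss, we are going to recruit 120 patients". The section prints neither a target difference in lactate nor an SD for pH, and it does not show how 0.02 pH units became a lactate difference.

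**The concern.** The threshold is in pH units, while the endpoint and the only spread given are in mmol/L. Something has to carry the threshold from one scale to the other, and the only candidate in the section is the correlation coefficient. That coefficient cannot do it. It is unitless, so multiplying 0.02 pH units by 0.77 gives another number on the pH scale. The lactate change that goes with a given pH change comes from the regression slope, r × SD(lactate) / SD(pH), and the section gives no SD for pH. Using r alone is right only if the two SDs happen to be numerically equal.

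At stake is the trial's only power statement for its primary outcome. If the conversion is invalid, the reader does not know what lactate effect this trial can detect, or whether that effect corresponds to the 0.02 pH units called clinically significant.

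**Working it through.** **Inputs.** From Sample size calculation: r = −0.77; pH threshold 0.02; lactate mean 2.0 with 0.028 in brackets (read as an SD in mmol/L); two-sided alpha 0.05; power 0.80; two-sample equal-variance t test; n = 53. From Randomization and blinding: 1:1 allocation. The article does not say that 53 is per arm, but 2 × 53 = 106 fits 120 recruited with an allowance for loss.

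**Reproducing the plan's figure.** Take δ = 0.77 × 0.02 = 0.0154 and d = δ / SD = 0.0154 / 0.028 = 0.55. The exact noncentral-t calculation for the named test gives n = 52.87, so 53 per arm (power 0.801 at 53, 0.793 at 52).

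**Other ways to combine the same inputs** (two-sided unless stated, SD 0.028):

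| δ used | n per arm |
|---|---|
| 0.77 × 0.02 = 0.0154 | **53** |
| 0.02 taken directly | 32 |
| 0.02 / 0.77 = 0.026 | 20 |
| 0.77 × 0.028 = 0.0216 | 28 |
| 0.0154, one-sided | 42 |

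Solving backwards, with SD 0.028 any δ from 0.01538 to 0.01553 returns 53. The product 0.0154 lies inside that narrow window. It also explains why a correlation is quoted at all.

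**What the number means.** Read as mmol/L, 0.0154 is 0.0154 / 2.0 = 0.77% of the stated mean. The article attaches no clinical meaning to a lactate difference of that size.

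**A valid conversion.** In magnitude, δ(lactate) = 0.77 × [SD(lactate) / SD(pH)] × 0.02. If the lactate SD in the slope and the lactate SD in the power calculation come from the same population, they cancel:

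d = 0.77 × 0.02 / SD(pH) = 0.0154 / SD(pH).

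The article gives no SD(pH), so the values below are assumptions.

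| Assumed SD(pH) | d | Power at 53 per arm |
|---|---|---|
| 0.028 | 0.55 | 80% |
| 0.03 | 0.513 | 74% |
| 0.04 | 0.385 | 50% |
| 0.05 | 0.308 | 35% |
| 0.06 | 0.257 | 26% |

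**When the SDs do not cancel.** Suppose the slope uses source-study SDs, assumed to be 0.5 mmol/L and 0.04 pH units, while the power calculation keeps 0.028. Then δ = 0.77 × (0.5 / 0.04) × 0.02 = 0.1925 mmol/L, d = 0.1925 / 0.028 = 6.9, and power is close to 100%. A hospital lactate SD larger than the source SD would push the other way.

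**The bracketed 0.028.** As an SD it implies a coefficient of variation of 0.028 / 2.0 = 1.4%. If it were instead a standard error from, say, 100 patients (an assumption), the SD would be 0.028 × √100 = 0.28, and power for 0.0154 mmol/L at 53 per arm would be about 6%.

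**What the size gives regardless.** At 53 per arm the detectable standardised difference at 80% power is about 0.55 SD, whatever the SD proves to be.

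**The case against.** The strongest objection is that the product is never printed. The article condenses a full protocol that is available on request, and the working may be set out there. That is fair as far as it goes: the multiplication is an inference and should be described as one. But the article does set out its inputs, test and result, and the result is recovered from those inputs only through this step. Even without the inference, a pH threshold, a correlation and a lactate SD cannot yield a lactate difference, because SD(pH) is missing.

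A second objection concerns size. A reader might infer from the table that the trial is underpowered and should have had between 61 per arm (SD(pH) 0.03) and 240 per arm (SD(pH) 0.06). The documents do not support that. Those figures need an assumed pH SD, and they also need both lactate SDs to come from one population. The article takes r from an outside study and the lactate figures from its own hospital. With mixed sources the power can rise or fall, so even the direction of the error is not established. This objection stands.

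A reader might also infer that a null result will be presented as ruling out a relevant effect. The article describes a difference test and makes no claim of equivalence or exclusion, so that is speculation.

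Finally, recruitment was expected to end on 31 December 2023, before the article appeared. This limits the practical remedy to correct reporting. It does not make the stated power right.

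**Conclusion.** The point holds in this form: the section states no lactate difference, its 53 per arm appears to come from treating a unitless correlation as a slope, and 80% power for the lactate equivalent of a 0.02 pH change is therefore unsupported. The match is exact (n = 52.87, rounded up to 53), and the natural alternatives miss widely. It rests on reading 53 as per arm and 0.028 as an SD in mmol/L.

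The effect on power cannot be fixed from the article. If the SDs share one population, 80% at 53 per arm requires SD(pH) of about 0.028 or less, and power falls to roughly 74% to 26% over the assumed range 0.03 to 0.06. Otherwise the change could go in either direction. What is established is that the power claim lacks a basis, not that the trial is too small. It still needs correcting, because it is the only power claim for the primary outcome.

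**What to change.** Rewrite the sample size paragraph:

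1. Remove the multiplication of r by the pH difference. State the target UA lactate difference directly in mmol/L and justify it clinically. Alternatively, convert 0.02 pH units with a regression slope, r × SD(lactate) / SD(pH), giving both SDs and their source.
2. Label the bracketed 0.028 and confirm from the hospital data that it is an SD, given the 1.4% coefficient of variation that it implies. If it is not, give the SD.
3. Say that 53 is per arm, if that is what is meant.
4. Keep 120 patients, and restate either the power for the justified difference or the detectable difference (about 0.55 SD at 53 per arm, expressed in mmol/L once the SD is confirmed).

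The cost is one reworded paragraph, a check of hospital records and a note that the justification was corrected. No patients are added. The restated power may be higher or lower than 80%.

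### The 0.028 mmol/L spread behind the sample size is not credible as a between-newborn SD of UA lactate, and the difference paired with it is not a lactate difference, so the stated 80% power is unsupported

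*Protocol article*

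**What the plan says.** The protocol article, under Sample size calculation, builds the number of patients from four statements:

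- A retrospective study is cited for the link between the two markers: "there was a strong inverse correlation between lactate and pH", with r = −0.77.
- The clinical threshold is given on the pH scale: "the clinically significant change of UA pH is assumed to be 0.02 pH units".
- The hospital's own experience supplies the lactate figures: "the mean of the UA lactate is 2.0 (0.028) mmol/l". The bracketed number is not labelled, and the number of newborns behind it is not given.
- The result is "and power of 0.80, the sample size was 53 according to a 2-side 2-sample equal-variance" t test, after "With a probability of *α* = 0.05". The total follows: "Considering 15% patient loss, we are going to recruit 120 patients".

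The primary outcome is UA lactate (Outcome assessment). No lactate difference in mmol/L is stated anywhere, and no other lactate SD appears in the article.

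**The concern.** Two inputs decide a two-sample t test sample size: the difference to detect and the between-subject SD. Here the only spread given is 1.4% of the mean, which is very small for a biological measurement across different newborns. The only threshold given is for pH, which is not the primary outcome. If either input is wrong, the claim of 80% power does not attach to any identifiable effect on lactate. A null result could then be read as good evidence that high-flow oxygen leaves lactate unchanged, with a power statement behind it that the design does not support.

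**Working it through.** **Inputs.** From Sample size calculation: two-sided α = 0.05, power 0.80, equal-variance t test, mean lactate 2.0, bracketed figure 0.028, r = −0.77, pH change 0.02, stated n = 53. From Randomization and blinding: "randomly assigned to the HFNO group or the air group at a ratio of 1:1".

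**1. Reproducing the 53.** Use the exact (noncentral t) two-sample calculation with SD = 0.028 and three candidate differences:

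| Candidate difference | Difference / SD | n per arm |
|---|---|---|
| 0.77 × 0.02 = 0.0154 | 0.550 | 52.87 → 53 |
| 0.02 | 0.714 | 31.76 → 32 |
| 0.02 / 0.77 = 0.0260 | 0.928 | 19.25 → 20 |

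Only the first returns the stated figure, with power 80.1% at 53 per arm. It uses every number in the paragraph, so it is very probably what was done: 0.028 entered as the SD and 0.0154 as the difference.

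**2. What an SD of 0.028 implies.** CV = 0.028 / 2.0 = 1.4%. The range 2.0 ± 2 × 0.028 is 1.944 to 2.056, so about 95% of newborns would lie between 1.94 and 2.06 mmol/L. The target would be 0.0154 / 2.0 = 0.8% of the mean. If 0.028 were instead a standard error from m newborns, the SD would be 0.028 × √m: 0.28 for m = 100 and 0.48 for m = 300 (m is assumed).

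**3. Why 0.0154 is not a lactate difference.** A correlation has no units. Converting a pH change to lactate needs the regression slope:

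lactate difference = |r| × SD(lactate) / SD(pH) × 0.02.

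Multiplying r by 0.02 sets the ratio of the two SDs to 1. Dividing the correct expression by SD(lactate) gives the standardised effect 0.77 × 0.02 / SD(pH) = 0.0154 / SD(pH). The lactate SD cancels, and power rests on the pH SD, which the article does not give.

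**4. Power at 53 per arm under each reading** (SDs other than 0.028 are assumed):

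| Target taken as 0.0154 mmol/L: lactate SD | Power |
|---|---|
| 0.028 | 80% |
| 0.05 | 35% |
| 0.10 | 12% |
| 0.50 | 5% |

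| Target taken as 0.02 pH units, converted by the slope: pH SD | Standardised effect | Power |
|---|---|---|
| 0.028 | 0.550 | 80% |
| 0.04 | 0.385 | 50% |
| 0.05 | 0.308 | 35% |

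**5. What the trial can detect.** At 53 per arm, 80% power corresponds to 0.549 SD. In mmol/L: 0.549 × 0.28 = 0.15, 0.549 × 0.50 = 0.27, 0.549 × 0.80 = 0.44 (SDs assumed). With all 120 analysed (60 per arm) the multiplier is 0.516. With 15% lost (120 × 0.85 = 102, or 51 per arm) it is 0.560.

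**The case against.** The strongest reply is that the loss of power has not been demonstrated. The article never states 0.0154 mmol/L. The stated 53 fixes only the ratio of difference to SD at 0.55, and an SD of 0.50 with a difference of 0.275 gives the same 53. If 0.028 is really a pH SD printed with the wrong unit, then on the pH anchor the standardised effect is 0.55 and the 80% survives whatever the lactate SD is. The trial also keeps 80% power for 0.55 SD in any case, and type I error and the primary comparison are unaffected.

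All of this stands, and it limits the claim. A reader might infer that the trial has essentially no power, but that follows only if 0.0154 mmol/L is the intended target and the lactate SD is much larger than 0.028. The documents establish neither.

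A reader might also see a contradiction with listing "the incidence of pH < 7.20 and pH < 7.10" as secondary outcomes, or with the Discussion's case for lactate as the more discriminating marker. Neither is a contradiction. Listing an outcome gives no expected incidence, and discrimination does not depend on the absolute scale of a marker.

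The reply does not rescue the paragraph as printed. The figure is given in mmol/l beside the lactate mean. Reading it as a pH SD requires a labelling error, and even then no lactate difference has been stated or justified.

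**Conclusion.** The concern holds in this form: the sample size rests on a spread that is not credible as a between-newborn SD of UA lactate, and on a difference that is not on the lactate scale. The 80% power claim for a clinically meaningful lactate difference is therefore unsupported.

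That 0.028 was used as the SD is a back-calculation, but a close one (52.87 against 53). That 1.4% is too small a CV is a judgement on plausibility, since the article offers no second SD to test it against. Whether the figure is a standard error, a pH-scale SD or a slip cannot be settled from the article.

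The size of the shortfall is accordingly conditional. It runs from none (0.028 is a pH SD and 0.02 pH units is the anchor) to nearly complete (0.0154 mmol/L is the target and the lactate SD is 0.10 or more). What can be said without choosing a reading is that 53 per arm detects 0.55 SD of lactate with 80% power, and that the article neither states nor justifies such a difference in mmol/L.

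**What to change.** - State what the 0.028 is (SD, standard error or other), on which scale, from which source and from how many newborns.
- Recompute the SD of UA lactate from the individual hospital values. Cross-check it against the pooled SD of enrolled patients, calculated without regard to arm; this compares no groups and costs no alpha.
- Remove the 0.77 × 0.02 step. Correcting the SD alone would leave a target that is not a lactate difference.
- Keep N = 120. Restate the difference detectable with 80% power in mmol/L, and justify on the lactate scale why a difference of that size matters.

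The cost is a query of existing hospital records, a blinded summary and one rewritten paragraph; no extra patients are needed. The article expected recruitment to finish by 31 December 2023, so the restatement should be fixed before any comparison between arms. The downside is that the stated detectable difference will look less favourable than the present text implies.

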### Statistical methods

Data analysis will be performed according to the modified intention-to-treat population. Moreover, the per-protocol analysis will be used as a sensitivity analysis. We expect very few patients to be lost. As a result, the missing data will be minimized when analyzing primary outcomes. Multiple imputation will be used to handle missing data if needed.

Shapiro–Wilk test is used to test normality. Quantitative indicator is expressed as mean ± standard deviation or median (interquartile range, IQR), while qualitative data is expressed as median (interquartile, IQR). Quantitative indicators are tested by independent sample *t* test or Mann–Whitney *U* test according to data distribution. Qualitative data is tested by the chi-square test/Fisher’s exact test. Statistical analysis will be performed by SPSS 27.0.

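### The target of 120 patients covers about 11.7% loss, not the stated 15%: at 15% loss 51 per group remain, two short of the calculated 53

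*Protocol article*

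**What the plan says.** The Sample size calculation section of the protocol article sets its error rates ("With a probability of *α* = 0.05, *β* = 0.2, and power of 0.80") and reports that "the sample size was 53 according to a 2-side 2-sample equal-variance" t test. It does not say whether 53 is per group or in total. The next sentence turns this into the target: "Considering 15% patient loss, we are going to recruit 120 patients". The Abstract and the Participants section repeat 120, and the Abstract and the Randomization and blinding section give 1:1 allocation, so the target is 60 per group.

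The Statistical methods section says "We expect very few patients to be lost" and provides for multiple imputation if it is needed. The article gives no other loss rate and no rule for replacing lost patients.

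**The concern.** Three figures stand together in one paragraph: a required size of 53, a loss allowance of 15% and a target of 120. Any two of them fix the third, and they do not agree. The paragraph tells the reader that 80% power survives a 15% loss. If it does not, the stated protection against loss is wrong even when every other assumption in the calculation is accepted. A reader who tries to reproduce the target will not reach 120.

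**Working it through.** **Inputs.** From the Sample size calculation section: calculated size 53; two-sided two-sample equal-variance t test; α = 0.05; power 0.80; loss 15%; target 120. From the Abstract and Randomization and blinding: 1:1 allocation.

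**Step 1: is 53 per group or in total?** The section gives a pH change ("the clinically significant change of UA pH is assumed to be 0.02 pH units"), a lactate–pH correlation of r = −0.77, and a lactate mean with a bracketed figure ("the mean of the UA lactate is 2.0 (0.028) mmol/l"). It states no lactate difference and does not label the bracketed figure as a standard deviation. As an assumption, take the difference as 0.77 × 0.02 = 0.0154 and the SD as 0.028:

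- standardised difference d = 0.0154/0.028 = 0.55
- smallest n per group with noncentral-t power of at least 0.80: n = 52 gives 79.3% and n = 53 gives 80.1%, so 53 per group.

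This reproduces the stated 53 as a per-group number. The other reading fails without any effect size: a total of 53 would need 53/0.85 = 62.4, about 63 recruits, which is nowhere near 120. The requirement is therefore 2 × 53 = 106 evaluable patients.

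**Step 2: inflate for 15% loss.** With n the evaluable number and L the loss proportion, recruits = n/(1 − L).

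- Per group: 53/0.85 = 62.35, so 63 per group and 126 in total.
- On the total: 106/0.85 = 124.7, so 125, which becomes 126 with equal arms.
- Check: 63 × 0.85 = 53.55, which is at least 53.

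The common but incorrect shortcut of multiplying by 1 + L gives 53 × 1.15 = 60.95 per group and 106 × 1.15 = 121.9 in total, so 61 per group or 122. This may be how 120 arose, by rounding down, but 120 falls short of this figure too.

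**Step 3: work back from 120.**

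- 120 × 0.85 = 102 evaluable, or 51 per group, against 53 required.
- Largest loss that keeps 106: 1 − 106/120 = 11.7%, that is 14 patients, or 7 of 60 per group if the losses are balanced.

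Steps 2 and 3 use only 53, 15% and 120. They do not depend on the value of d.

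**Step 4: what it costs in power.** Because d is not stated, take every d for which 53 is the smallest adequate group size. That interval runs from about 0.549 (power exactly 80% at 53) to about 0.555 (power exactly 80% at 52).

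| d | 51 per group | 53 per group | 60 per group |
|---|---|---|---|
| 0.549 | 78.4% | 80.0% | 84.7% |
| 0.550 | 78.5% | 80.1% | 84.8% |
| 0.555 | 79.2% | 80.8% | 85.4% |

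At the full 15% loss, power is 0.8 to 1.6 percentage points under the stated 80%.

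**The case against.** The strongest reply is that this hardly matters. The shortfall is six recruits, or two evaluable patients per group, and it arises only if the whole allowance is used. With little loss, 60 per group gives power of about 85% on the same assumptions. No test, analysis set or conclusion changes. All of this stands, and it is why the point is minor. It does not make the sentence right, because 53, 15% and 120 still do not fit together.

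A second reply is that the provision for multiple imputation deals with loss. Imputation does not restore the planned number of observed outcomes, and the sample size section itself handles loss by recruiting more.

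A third is that 53 is not labelled as per group and that the effect size is a reconstruction. Both are true, and both are marked as inferences above. The per-group reading is the only one compatible with 120, and the inflation error does not use the effect size.

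A reader might go further and infer that a 15% allowance contradicts the Statistical methods section, where "We expect very few patients to be lost". The documents do not support that. A planning margin may sit above the loss that is expected, and cautious planning usually does this. The 15% might also be meant to cover exclusions from the modified intention-to-treat or per-protocol sets, although the article does not say so. The expectation of few losses in fact suggests that the smaller allowance will be enough.

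**Conclusion.** The point holds as a minor arithmetic correction. On the section's own figures, 15% loss needs 126 patients, and 120 patients cover at most 11.7%. The conclusion rests on reading 53 as per group, which the text does not state but which no other figure in the paragraph permits otherwise. The power statement, 78.4% to 79.2% at 51 per group, rests further on 53 being the smallest adequate size under an unstated effect.

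It would be tempting to conclude that the trial is underpowered. The documents do not support that: the deficit appears only if losses exceed 11.7%, and it is then under two percentage points at the stated 15%. Whether the effect size behind the 53 is sound is a separate question, and this point neither relies on it nor settles it.

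**What to change.** Keep 120 and replace the 15% figure in the Sample size calculation section with wording such as: *53 patients per group are required; 120 patients (60 per group) allow for up to about 11.7% loss (7 per group).* This also supplies the missing per-group label. A power figure at 15% loss should not be added, because it would depend on a lactate difference that the protocol does not state.

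The alternative, keeping 15% and recruiting 126, is also arithmetically correct but is less practical: under Trial status, recruitment was expected to end on 31 December 2023, before publication on 22 January 2024.

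The cost is one sentence and a slightly less favourable stated allowance, with no extra patients. The Statistical methods section needs no change on this account.
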